Preoperative psychological risk factors for the development of POCD include depression (7, 8) and reduced neuropsychometric functions (9). Preexisting cognitive impairment may also contribute to the development of dementia (10). In addition, depression (11), preoperatively reduced objective cognitive functions (11), or reduced cognitive everyday activities such as reading, writing, solving crosswords, and playing computer games (12) could be linked to the development of POD. Furthermore, in a rat model, it was shown that a preoperative enrichment of activity opportunities can lower the rate of POCD (13). In summary, diminished neuropsychometric functions or reduced cognitive everyday activities can be declared as a lower cognitive reserve. In the classical sense, the term “cognitive reserve” refers to the adaptability of cognitive processes, which can help to explain the sensitivity of cognitive abilities or everyday functions in the context of physiological aging and pathological neurodegeneration of the brain. The cognitive reserve can be influenced, among other things, by general cognitive ability in early life (intelligence), education, occupation, physical activity, leisure activities, or social engagement (14). For example, it has been shown that increased cognitive or social leisure activities performed within a wide life span (childhood to adulthood) can reduce the risk of developing dementia (15, 16). Increasing the cognitive reserve through focused cognitive training may, therefore, be a potential intervention target to prevent postoperative neurocognitive dysfunctions.

The primary objective of this study is to investigate the interventional effect of preoperative cognitive training on the incidence of POD during the stay in the acute clinic, the incidence of POCD at the time of discharge from the acute clinic, and 3 months after surgery. Secondary objectives are to determine the training effect on objective cognitive functions before the surgery and subjective cognitive functions, as well as health-related quality of life 3 months after surgery.

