### Primary outcomes

Number of participants with POCD at 3 months after surgery.Number of participants with POCD at the time of discharge from the acute clinic.Number of participants with POD during the stay in the intensive care unit.Number of participants with POD during the stay in the normal ward.

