If peri- and postoperative complications such as delirium, stroke, cardiovascular events, or other complications occur which could affect neuropsychological performance, and if these factors are unbalanced between the groups, we will calculate a subgroup analysis without those patients to reveal a more stringent outcome effect. In addition, we will perform subgroup analyses for each of the individual surgery cohorts, including AVR, MVR, CABG, and combination surgeries (AVR+MVR, CABG+AVR, CABG+MVR, and CABG+AVR+MVR) if the sample size of these subgroups allows for statistical analysis. Perioperative medical conditions or drug factors may have an impact on cognitive function. With the randomization principle, we expect these to be equally distributed between the groups. Otherwise, if the groups differ with respect to these factors, these can be accounted for in a subgroup analysis.

All analyses will be performed using the statistical software SPSS (version 22) and JASP (version 0.12.2).

Furthermore, interim analyses will be carried out during the investigation period to identify adverse events, overwhelming effects, or futility of the intervention arm. In this case, the study could be terminated before its planned completion. The decision will be made by the members of the study team.

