## Discussion

This research project offers our patients preoperative cognitive training based on paper-and-pencil aiming to prevent POD and POCD.

Investigations have already been conducted to treat the preoperative physical condition of cardiosurgical patients to improve postoperative outcomes, which is defined by the term prehabilitation (42). Initial efforts have also been made with regard to preoperative cognitive training. Saleh et al. showed a lower incidence of POCD 1 week after gastrointestinal tumor resection with a controlled 3 x 1-h preoperative memory strategy training (loci method) (43). Several studies have investigated the effect of perioperative computer-based cognitive training on postoperative cognition after cardiac surgery. In the study conducted by O'Gara et al. (44), the training was performed at least 10 days before surgery up to 4 weeks postoperatively, which had no significant effect on the frequency of POD or POCD. Humeidan et al. found a reduced incidence of POD with preoperative computer-based cognitive training (median 4.6 h) (45). Vlisides et al. showed that participation in preoperative computer-based cognitive training was difficult for older adults who underwent surgery (46). Mainly because of the feeling of overwhelming demands and technical problems with the 7-day computer exercises, 48% of the patients discontinued the training.

The difference in our study concept compared with the above-mentioned studies is that we use paper-and-pencil-based instead of computer-based cognitive training, which is probably more feasible and effective for older patients. Furthermore, our program will take place in the preoperative phase, which will help to address differences between preoperative and [as we have conducted in the past; (39)] postoperative training. As we saw in the postoperative setting, this cognitive training appears to be adequately feasible regardless of educational status. Therefore, we did not set a limit for a required educational status in the inclusion criteria.

Cognitive training allows patients to be independent, responsible, and active. With the knowledge that cognitive deficits can be actively prevented, anxiety regarding a severe operation can be reduced. This has particular clinical relevance, as preoperative anxiety is considered a risk factor for increased morbidity and mortality in cardiac surgery patients (47).

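### A supplementary analysis drops patients with delirium, itself a primary outcome, when the arms differ on it, and presents the result as the stricter estimate

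*Protocol article*

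**What the plan says.** The Planned statistical analyses section compares POCD and POD between arms by chi-square or Fisher's exact test, and the cognitive tests by ANCOVA with the preoperative value as covariate. Neither carries an exclusion for complications. The section then adds a conditional analysis. Its condition is that "peri- and postoperative complications such as delirium, stroke, cardiovascular events, or other complications occur which could affect neuropsychological performance", and it continues: "if these factors are unbalanced between the groups, we will calculate a subgroup analysis without those patients to reveal a more stringent outcome effect". For perioperative medical conditions and drug factors it first relies on randomisation for balance and then says: "Otherwise, if the groups differ with respect to these factors, these can be accounted for in a subgroup analysis".

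The Primary outcomes section lists "Number of participants with POD during the stay in the intensive care unit" and "Number of participants with POD during the stay in the normal ward". The Discussion describes the intervention as "preoperative cognitive training based on paper-and-pencil aiming to prevent POD and POCD". Under Study process, randomisation comes before training and surgery, so every event in the list happens after randomisation.

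**The concern.** The trigger is a difference between arms in an event that training is intended to change. If training prevents delirium, the trigger is more likely to be met, and more patients leave the control arm than the training arm.

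The patients who leave are not a random sample. The Introduction gives the reason. For POCD: "Preoperative psychological risk factors for the development of POCD include depression (7, 8) and reduced neuropsychometric functions (9". For POD it names "depression (11), preoperatively reduced objective cognitive functions (11), or reduced cognitive everyday activities". Depression and reduced preoperative cognition are thus risk factors for both. Delirium-free controls are those who escaped delirium unaided. Delirium-free trained patients also include those who escaped it only because they trained, and who may still be prone to decline.

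Two things go wrong in the reduced comparison: any benefit that acts through less delirium is removed by construction, and the arms are no longer balanced on vulnerability. A reader told that this is the stricter result would give it more weight than the randomised comparison, when it deserves less.

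**Working it through.** **The plan's own figure.** With f = 0.65/2 = 0.325, a two-group ANCOVA with one covariate has power 0.804 at N = 77 (two-sided alpha 0.05), and 77/(1 - 0.23) = 100. The stated 77 and 100 reproduce. The exclusion rule does not affect them; 77 is used below only to count patients, split 39 and 38.

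**Inputs from the document.** POD after cardiac surgery 14% to 50%; POCD 28% between months 1 and 4 (Introduction).

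**Assumed inputs.** Training halves POD. The POCD risk of delirious patients, the risk kept by patients spared delirium, the cognitive cost of delirium and the strength of shared vulnerability are not in the document.

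**Patients lost to delirium alone, at 30% versus 15%.** 39 x 0.30 + 38 x 0.15 = 11.7 + 5.7 = 17.4, leaving about 60 of 77 (27.3 control, 32.3 training).

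**POCD as an odds ratio (below 1 favours training).** Let POCD risk be 50% in delirious patients.
- Never-delirious patients: (0.28 - 0.30 x 0.50)/0.70 = 0.186.
- Patients spared delirium by training, taken midway: (0.50 + 0.186)/2 = 0.343.
- Training arm, all patients: 0.15 x 0.50 + 0.15 x 0.343 + 0.70 x 0.186 = 0.256, against 0.28 in control. OR 0.89.
- Training arm, delirium-free: (0.15 x 0.343 + 0.70 x 0.186)/0.85 = 0.213, against 0.186 in control. OR 1.19.

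The same steps across the document's POD range:

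| POD, control to training | POCD if delirious | All patients, training vs control | Delirium-free, training vs control |
|---|---|---|---|
| 14% to 7% | 50% | 27.1% vs 28%, OR 0.96 | 25.4% vs 24.4%, OR 1.05 |
| 30% to 15% | 50% | 25.6% vs 28%, OR 0.89 | 21.3% vs 18.6%, OR 1.19 |
| 50% to 25% | 40% | 25.0% vs 28%, OR 0.86 | 20.0% vs 16.0%, OR 1.31 |

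Two variations on the middle row show how far this depends on the assumptions:
- If spared patients return fully to the low risk, OR 0.78 becomes 1.00: the benefit disappears but does not reverse.
- If training also cuts POCD risk by 40% in never-delirious patients, OR 0.66 becomes 0.79: attenuation only.

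**Continuous scores under the planned ANCOVA (simulation).** Assumptions: delirium log-odds rise by 1.0 per SD of a latent vulnerability that correlates -0.5 with postoperative cognition; pre-post correlation 0.6 to 0.8; delirium costs 0.8 SD; no direct training effect.
- True total effect: 0.8 x (0.30 - 0.15) = +0.12 SD. The all-patient ANCOVA recovers it.
- Delirium-free ANCOVA: about -0.01 to -0.02 SD if vulnerability acts equally on both time points, and -0.03 to -0.04 SD if it acts more strongly after surgery (correlation -0.3 before, -0.5 after).
- At 50% versus 25% the true effect is 0.8 x 0.25 = +0.20 SD. The delirium-free ANCOVA gives about -0.02 to -0.04 SD in the equal case and -0.05 to -0.06 SD in the stronger case.
- Change scores after exclusion: 0.00 to -0.04 SD.
- With a direct effect of 0.3 SD, at 30% versus 15%, the true 0.30 + 0.12 = +0.42 SD becomes about +0.26 to +0.28 SD.

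The part below zero is selection: setting the cognitive cost of delirium to zero leaves it almost unchanged.

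**The case against.** **It is an added analysis.** A reader might infer that these patients are removed from the primary comparison. The document does not say so. It calls the exclusion a subgroup analysis, and the tests planned for all patients carry no such restriction. This stands, and it limits the point to how the extra analysis is triggered and described.

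**Sign reversal.** A reader might infer that the rule will generally reverse the training effect. That is not supported. Comparing raw postoperative scores, exclusion gives -0.06 SD at 30% versus 15% and -0.10 SD at 50% versus 25%, but the plan adjusts for the preoperative score and defines POCD by change, which removes much of this. In a grid of 72 POCD scenarios the sign reversed in 26; the grid was chosen, so that is not a probability. With about 60 patients the unadjusted standard error is near 2/sqrt(60) = 0.26 SD, so a shift of a few hundredths of an SD lies well inside the noise. The loss of delirium-mediated benefit is the firmer result.

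**The trigger may not fire.** No criterion for imbalance is given. If it meant p < 0.05 by chi-square (an assumption), it would fire about 34% of the time at 30% versus 15% and about 64% at 50% versus 25%. This limits how often the problem arises, but it arises most when training works on delirium.

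**Scope.** The Power and sample size estimation section powers only the cognitive change at the end of training, which precedes surgery, and calls the POD and POCD analyses exploratory. This stands. An exploratory result can still mislead if the less reliable analysis is offered as the more rigorous one.

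**Medical and drug factors.** The wording is permissive, and these factors are not presented as targets of training; a difference may be chance. They cannot be put on a par with delirium.

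**Conclusion.** The rule is wrong as written, within a limited scope. It selects on a primary outcome after randomisation, is triggered by what may be the treatment effect, and labels the result as stricter. It bears on POCD and the 3-month cognitive tests, not on the powered preoperative outcome, and the randomised comparison remains available beside it.

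Under the planned ANCOVA, with POD 30% versus 15%, a 0.8 SD cost of delirium and no direct effect, a true +0.12 SD becomes about -0.02 to -0.04 SD (about -0.01 SD in the most favourable setting tried). The removal of benefit acting through delirium held in every setting examined where delirium affects cognition. A material reversal depends on assumptions the document does not supply: little direct effect, and residual vulnerability in patients spared delirium.

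**What to change.** In Planned statistical analyses:
- Delete the imbalance trigger and the closing clause that presents the result as stricter.
- State that inference on training rests on all randomised patients with data.
- Report complications by arm as outcomes.
- Label any complication-free analysis as descriptive and not as an estimate of the training effect.
- Replace the sentence on medical and drug factors: adjust only for variables measured before randomisation (for example age, education, first-examination score, planned surgery type), and do not form subgroups because the arms differ. The ANCOVA covariate rule in the same section admits perioperative details and needs the same limit.

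The cost is a few sentences. No new data are needed, and the change should be made before results by arm are seen.

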### Randomization

Randomization will be implemented using a computer-generated randomization list (www.randomization.com) with a 1:1 blocked allocation ratio and block sizes of 10. The randomization list will be generated, sequentially numbered, and concealed before the start of the study by the randomization list holder, who is located in the department of Neurology at the University Hospital Giessen and Marburg. After recruitment and the first preoperative neuropsychological examination, a study coordinator will allocate patients to the cognitive training or control group. A study coordinator will inform the psychological training supervisor about which patients should be trained.

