### Power and sample size estimation

Because there are currently no effect sizes for extensive paper-and-pencil-based preoperative cognitive training in cardiac surgical patients using extracorporeal circulation, and because their influence on the incidence of POD and POCD is unclear, we have estimated sample size based on the effect sizes of general cognitive training in older healthy individuals, which ranges between d = 0.4 and d = 0.9 (20, 21). To not underestimate or overestimate the required sample size, we use an average value of d = 0.65. To find an effect size of d = 0.65 at a test power of 0.8 (alpha = 0.05) within an ANCOVA, a sample size of 77 subjects is required. With an estimated dropout rate of 23% in the preoperative test phase, the total sample size will be 100 subjects. The sample size per group is thus 50 patients. We used the analysis software G^*^Power-3 to calculate the sample sizes and the statistical power (22). We want to note that the power analysis refers to our secondary outcome “Changes from baseline neuropsychological parameters at the end of cognitive training.” Accordingly, the primary outcomes regarding the incidence of POD and POCD will be calculated exploratively.

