Morphological alterations have also been found in response to cognitive training in healthy adults with reproducible increased patterns in the structure of gray and white matter (48) and patients with memory impairments, with increased volume of gray matter in certain brain regions (49). These effects are mainly attributed to cognitive and neuronal plasticity.

The limitations of this study are as follows. The study only includes patients undergoing cardiac surgery with ECC. A comparison with patients undergoing off-pump cardiac surgery, non-cardiac surgery, or non-surgery (healthy controls) is, therefore, not intended. A placebo intervention for the control group is intentionally avoided because the cognitive effects of placebo interventions on cognitive performance are hardly controllable. To convincingly communicate to patients that the placebo intervention could have an influence on their memory and thus also achieve a willingness to participate, the structure of the placebo intervention would have to be closely related to cognitive training (e.g., crossword puzzles, conversation therapy, computer games, cognitive information, etc.) and would thus also achieve cognitive training effects. This could formally affect the quality of the study and the transferability of the results. As we do not know whether paper-and-pencil-based preoperative cognitive training can reduce the incidence of POD and POCD, we do not see any ethical problems if the control group does not receive cognitive training. Finally, in principle, it may be that cognitive intervention proves useless and that patients' preoperative time would be better spent on other validated and clinically relevant interventions. Furthermore, according to our study design, it is not possible to put the patients of the control group on a waiting list, as they would have already been operated on. If a subgroup analysis for each cardiac surgery method (CABG, AVR, MVR, and combination surgeries such as AVR + MVR, CABG + AVR, CABG + MVR, and CABG + AVR + MVR) is statistically inadequate due to the small sample size, we cannot adequately perform generalization of the training effect on a single surgery cohort.

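### Surgery-type effects are to be analysed cohort by cohort with no group-by-surgery interaction, so within-cohort significance could be misread as a claim about one operation or a difference between operations

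*Protocol article*

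**What the plan says.** Protocol article, Planned statistical analyses: "we will perform subgroup analyses for each of the individual surgery cohorts". The cohorts named are AVR, MVR, CABG and combination surgeries, with four combinations listed in brackets. This can be read as four cohorts (combinations pooled) or seven (each combination separate). The analyses are conditional on adequate cohort size, but no threshold is stated.

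The models in the same section contain no interaction. The ANCOVA has group as its fixed factor and the preoperative value as covariate, and other variables can enter only as further covariates. POCD, POCI and POD are compared by chi-square or Fisher's exact test.

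Discussion, limitations: if the cohort analyses are inadequate because numbers are small, "we cannot adequately perform generalization of the training effect on a single surgery cohort".

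Randomization is "with a 1:1 blocked allocation ratio and block sizes of 10", with no stratification by surgery type mentioned. Power and sample size estimation ties the calculation to the cognitive change at the end of training and calls the analysis of the primary outcomes exploratory.

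**The concern.** A separate analysis in each cohort asks whether training has an effect in that cohort. It does not ask whether the effect depends on the operation. When the whole trial has just enough patients to detect the planning effect, each cohort has far too few. An effect that is identical across operations will then often be significant in some cohorts and not in others.

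The limitation in the Discussion makes cohort size the only barrier to a single-surgery claim. Size alone does not cure the problem: a significant result in CABG and a non-significant one in AVR is not evidence that the two differ. The risk is that a published table of within-cohort p-values is taken to show that training works for one operation and not for another.

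**Working it through.** **Inputs from the article (Power and sample size estimation).** On the effect size: "we use an average value of d = 0.65". Power is set at 80% with a 5% alpha, for which the article gives 77 evaluable patients. It then allows for 23% dropout and arrives at 100 in total.

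**The plan's own figure.** With f = d/2 = 0.325, λ = f²N and df = 1, N − 2 − (number of covariates), the smallest N with at least 80% power is 77. There λ = 0.1056 × 77 = 8.13 and power is 0.804. Using 0, 1, 2 or 5 covariates does not change N. Dropout: 77 / (1 − 0.23) = 100. Both stated numbers reproduce.

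**Assumptions.** Cohort shares are not in the article, so several were tried. The true effect is d = 0.65 in every cohort. Arms are equal within cohorts, with n per arm rounded from N × share / 2. Tests are two-sided at 0.05.

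**Power within a cohort.** Noncentral t with 2n − 2 df and noncentrality 0.65 × √(n/2). For example, n = 10 per arm gives noncentrality 1.45 and power 28%.

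**Chance of a mixed pattern** (at least one cohort significant and at least one not): 1 − ∏pᵢ − ∏(1 − pᵢ). Four equal cohorts at N = 77: 1 − 0.28⁴ − 0.72⁴ = 1 − 0.006 − 0.269 = 72.5%.

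| Assumed shares | Power per cohort, N = 77 | Mixed | Power per cohort, N = 100 | Mixed |
|---|---|---|---|---|
| four equal | 28% each | 73% | 33% each | 79% |
| 50/25/10/15 | 50, 28, 12, 18% | 73% | 62, 33, 15, 23% | 82% |
| 40/30/10/20 | 41, 33, 12, 23% | 73% | 52, 41, 15, 28% | 82% |
| 60/20/5/15 | 58, 23, 7, 18% | 75% | 70, 28, 7, 23% | 84% |
| seven equal | 18% each | 74% | 20% each | 79% |

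**Only the two largest cohorts analysed.** Shares 50/25 at N = 77: 1 − 0.496 × 0.280 − 0.504 × 0.720 = 1 − 0.139 − 0.363 = 50%. The same formula over the three uneven splits and both values of N gives 47% (40/30, N = 77) to 59% (60/20, N = 100), that is, roughly half.

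**No effect anywhere.** At least one significant cohort: 1 − 0.95⁴ = 18.5% with four cohorts and 1 − 0.95⁷ = 30.2% with seven, per outcome.

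**Interaction test instead.** In 20,000 simulated trials per setting, with four or seven cohorts and no true difference between them, the group-by-cohort F test declared a difference in 4.7% to 5.3%.

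**Precision of the interaction.** For two cohorts with n per arm, the difference between their training effects has standard error √(4/n) in SD units. At n = 10 this is 0.63, so the 95% CI is about ±1.24 SD. At n = 12 it is 0.58, or ±1.13 SD. Both half-widths are well above the planning effect of 0.65.

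**Binary outcomes.** The Introduction gives 14% as the lower POD rate and 28% for POCD between the first and fourth month. Take four equal cohorts (about 9.5 patients per arm and cohort) and the same rate in both arms. The chance that at least one of the eight arm-by-cohort cells has no events is 1 − (1 − 0.86^9.5)⁸ = 89% at 14%, and 1 − (1 − 0.72^9.5)⁸ = 30% at 28%. An empty cell leaves that cohort's odds ratio, and so the logistic interaction, without a usable estimate.

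**The case against.** The strongest reply is that the article announces no comparison between cohorts. It names no test or decision rule for the cohort analyses. The sentence in the limitations is a disclaimer, and details may sit in a fuller protocol or analysis plan that is not shown. Much of this stands. A reader might infer that the plan intends to declare training effective for one operation and not another, or that chance is bound to make cohorts look different. The text supports neither: no contrast is stated, and the mixed pattern is likely under the assumptions, not certain. What remains is that the article commits to analyses within each cohort, specifies models without an interaction, and leaves small numbers as the only stated reason for withholding a single-surgery claim. That is a stated approach, not mere silence.

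A reader might also take one high percentage as a property of this trial. It is not. The shares are assumed, the size condition may remove the smallest cohorts, and d = 0.65 belongs to cognitive change at admission, usually the day before surgery. The article gives no effect size for POCD or POD, so the power and mixed-pattern figures do not describe those outcomes.

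Multiplicity over the many neuropsychological parameters is a separate matter, and an interaction test on each parameter would share it. The objection that an interaction test is weak at this sample size, and fragile for binary outcomes, is correct and limits the remedy.

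**Conclusion.** The point holds as a minor one about interpretation. Separate cohort analyses cannot show whether the training effect depends on surgery type, and the limitation as worded leaves room for single-cohort claims that rest on them. Under a uniform d = 0.65 and the assumed shares, a mixed pattern would appear in about 50% of trials (two largest cohorts) to 84% (all cohorts, N = 100), against about 5% false declarations from an interaction test. Under no effect, 18.5% of trials would show at least one significant cohort out of four, per outcome. The direction of the finding is the same over every split tried, but the exact percentages depend on shares that the article does not give. The overall group comparison, the sample size and the exploratory status of the primary outcomes are unaffected.

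**What to change.** - **Continuous outcomes:** add surgery type and a group-by-surgery-type term to the ANCOVA. Define the categories in advance (for example, combination surgeries pooled), and report the interaction estimate with its CI. The Mann–Whitney fallback has no direct equivalent, so give cohort differences as description there.
- **POCD and POD:** fit the interaction in a logistic model only where event counts allow. Otherwise give event counts per arm and cohort, and estimates with 95% CIs.
- **Wording:** in Planned statistical analyses, label all cohort results descriptive. There and in the Discussion limitations, state that no claim about a single cohort, or about a difference between cohorts, rests on within-cohort p-values.

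Cost: a few sentences of analysis text and, with four categories, a 3-df interaction in each model where it is fitted. No new data and no change in conduct. The downside is low power at 77 to 100 patients, so the report should say that a non-significant interaction does not show equal effects.

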## Methods and analysis

### General conditions

The planned research project is a monocentric, randomized controlled study conducted by the Heart and Brain Research Group—a cooperation project between the Department of Cardiac Surgery of the Kerckhoff Heart and Thoracic Center in Bad Nauheim and the Department of Neurology of the University Hospital Giessen. Our working group consists of members of the Departments of Neurology, Neuropsychology, Radiology, and Cardiac Surgery who are responsible for the study procedure, including preparing the protocol, monitoring the study, and writing the study reports. This study protocol follows the Standard Protocol Items: Recommendations for Interventional Trials (SPIRIT) guidelines (17). The data monitoring committee was not believed to be necessary, as no adverse effects of cognitive training are expected.

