### Blinding

Neuropsychologists and nursing staff who will be involved in the assessment of outcome variables will be blinded for randomization status. The training sessions will be conducted by a psychological training supervisor who is not involved in the evaluation of outcome parameters to ensure blinding. The holder of the randomization list is not involved in the supervision of the training or the evaluation of all examinations on neuropsychometrical functions and delirium. In addition, the randomization list and its holder are located in the department of Neurology at the University Hospital in Giessen where the psychological evaluations, the intervention, and the surgery do not take place. Furthermore, when we inform patients by mail about which randomization group they are assigned to, we instruct them for all subsequent assessments not to inform the investigators about their randomization status.

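### The study team itself may stop the trial for efficacy or futility, with no independent body and no boundary stated in the article, so error control and assessor blinding are not assured

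*Protocol article*

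**What the plan says.** All of this is in the protocol article.

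- Planned statistical analyses: "interim analyses will be carried out during the investigation period to identify adverse events, overwhelming effects, or futility of the intervention arm". The consequence follows: "In this case, the study could be terminated before its planned completion". So does the decision-maker: "The decision will be made by the members of the study team". The article gives no number or timing of looks, no outcome to be monitored and no boundary.
- General conditions: "The data monitoring committee was not believed to be necessary, as no adverse effects of cognitive training are expected". The same section makes the working group responsible for monitoring the study and describes its make-up: "Our working group consists of members of the Departments of Neurology, Neuropsychology, Radiology, and Cardiac Surgery".
- Blinding: "Neuropsychologists and nursing staff who will be involved in the assessment of outcome variables will be blinded for randomization status". Training supervision, outcome assessment and custody of the randomization list are kept in separate hands. No similar separation is described for interim results.
- Power and sample size estimation: 77 evaluable patients, calculated "at a test power of 0.8 (alpha = 0.05) within an ANCOVA", and 100 in total after 23% dropout. The calculation belongs to a secondary outcome, neuropsychological change at the end of training. The primary outcomes (delirium and cognitive decline) are declared exploratory.

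**The concern.** An overwhelming effect, or futility of one arm, can be judged only by comparing the arms. The article therefore plans comparative looks that may end the trial, and gives the decision to those who run it.

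Three things are at stake.

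1. **Error control and estimates.** Each efficacy look that can stop the trial is another chance of a false positive unless the thresholds allow for it. A trial stopped at a chance high also overstates the effect. That matters for the primary outcomes too, exploratory or not, because they are to be reported as odds ratios with 95% confidence intervals.
2. **Independence.** The reason for having no committee concerns adverse effects alone. It does not explain why efficacy and futility decisions need no independent body. It also conflicts in spirit with looks intended partly to find adverse events.
3. **Blinding.** The working group includes Neuropsychology, and neuropsychologists perform the cognitive tests. If assessors learn the interim results by arm, their expectations may colour later ratings. The delirium instruments rest partly on observed behaviour.

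**Working it through.** **Step 1. Reproduce the planned sample size.** Inputs from Power and sample size estimation: "we use an average value of d = 0.65", power 0.80, alpha 0.05, ANCOVA. Assumed, because not stated: a two-sided F test with two groups and one covariate.

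- f = d/2 = 0.65/2 = 0.325.
- Noncentrality λ = f² × N = 0.105625 × N, with 1 and N − 3 degrees of freedom.
- N = 76 gives power 0.798. N = 77 gives λ = 8.13 and power 0.8036. The smallest adequate N is 77, as stated.
- Dropout: 77/(1 − 0.23) = 100, as stated.
- A one-sided test would need about 60, so the two-sided reading is the one that fits.

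Both figures reproduce with the full 0.05 used at a single analysis, so the stated N shows no allowance for interim looks. It cannot exclude one either: a two-analysis O'Brien-Fleming design needs 78 evaluable patients, one more.

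**Step 2. Type I error under repeated analyses.** The article gives no number of looks and no rule, so a range is needed. Assume K analyses in all, including the final one, at information fractions t = 1/K, 2/K, …, 1. Under the null, the statistics Z₁, …, Z_K are standard normal with correlation √(t_j/t_k) for j < k. The overall error is P(|Z_k| ≥ c_k for at least one k), obtained by recursive numerical integration.

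| Analyses K | p<0.05 at every analysis (c = 1.96) | Interim p<0.001 (c = 3.29), final 0.05 |
|---|---|---|
| 2 | 0.083 | 0.0502 |
| 3 | 0.107 | 0.0505 |
| 4 | 0.126 | not computed |
| 5 | 0.142 | 0.0511 |
| 10 | 0.193 | not computed |

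Only efficacy looks enter this table. Non-binding futility looks and adverse-event reviews do not raise the efficacy error.

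**Step 3. What a formal boundary would need (overall two-sided 0.05, power 0.80).**

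| Boundary | K | Nominal p | Evaluable N | Total with 23% dropout |
|---|---|---|---|---|
| O'Brien-Fleming | 2 | 0.0052, then 0.0480 | 78 | 102 |
| O'Brien-Fleming | 5 | 0.0413 at the final analysis | 80 | 104 |
| Pocock | 2 | 0.0294 at each | 86 | 112 |
| Pocock | 5 | 0.0158 at each | 95 | 124 |

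A strict boundary costs almost nothing; a lenient one needs 12 to 24 more patients than the planned 100.

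**Step 4. Set the monitoring passages side by side.** General conditions waives a committee because no adverse effects are expected. Planned statistical analyses then schedules looks for adverse events, efficacy and futility, and names the study team as the one to decide. The waiver does not reach two of those three purposes and is at odds with the third. Blinding protects assessors from knowing a patient's allocation, but neither it nor the interim paragraph says who prepares or sees results by arm.

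**The case against.** The strongest reply has four parts.

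- **This is an article.** The number of looks, the boundary and any alpha spending may be in a full protocol or analysis plan that is not shown. That stands: their absence here does not prove that they were never set. But the article does fix who decides, the waiver of a committee and the reason for the waiver. A later document would have to overrule this text to change them.
- **A reader might infer that the 0.05 level is broken.** The documents do not support that. The 8.3% to 14.2% figures require stopping at unadjusted p<0.05, a rule stated nowhere, and the word overwhelming suggests something stricter. With interim p<0.001 the inflation is negligible. What can be said is that control is not assured.
- **No confirmatory error rate is claimed for the primary outcomes.** This also stands. The only stated alpha belongs to a secondary outcome, and nothing says that all four primary outcomes are monitored, so no multiplied error rate can be attached to them. Exaggerated estimates after an early stop remain a problem, and with no confirmatory primary outcome an efficacy stop is harder to justify.
- **A reader might infer that blinded assessors do see results by arm.** No section says so. Listing Neuropsychology in the working group does not place the assessing neuropsychologists among those who decide, and aggregate results do not reveal a given patient's arm. The risk is expectation bias, plus exposure to arm-coded data if the team runs the comparison itself. The text leaves that route open.

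**Conclusion.** The point holds as a defect in what the article states. Efficacy and futility stopping is placed with the study team, without an independent body, and the stated reason for having none does not cover such decisions.

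For the powered secondary outcome, control at 0.05 is not assured. The error lies at about 5.0–5.1% under a strict interim rule with two to five analyses. Under unadjusted 0.05 testing it is 8.3% with two analyses and 14.2% with five. The range rests on assumed equally spaced analyses, a two-sided test and an assumed stopping rule. The documents do not show where in it the trial lies.

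For the exploratory primary outcomes the harm is exaggerated odds ratios after a stop on a chance high; its size cannot be given without a rule. For blinding, assessors may see arm-level results because nothing excludes them. It is not established that they do.

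**What to change.** Preferred: delete the efficacy and futility looks and keep a review of adverse events pooled over arms. With 100 patients, an intervention expected to have no adverse effects and exploratory primary outcomes, there is little reason to stop early.

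If a look is kept, write down:

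- one look, at half the planned patients (50 of 100), on one named outcome;
- an efficacy stop only at p<0.001, with the final test at about 0.05 (overall error 0.0502 if that look falls at half the information);
- futility as non-binding;
- that the comparison is run by someone with no role in training or assessment;
- that outcome assessors do not see arm-level results.

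The randomization list holder meets the separation from training and assessment, but belongs to a department represented in the working group and is not described as a statistician. Someone further removed would be better.

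The Trial status section says that enrolment began in August 2020 and was still open, so any look already done should be reported, with what was compared and who saw it.

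Cost: the team gives up ad hoc early stopping, and the change must go to the Ethics Committee, as the Ethics statement requires of all protocol changes. Neither option needs more patients.
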